### Sample size

Complementary to the new study design for clinical trials presented in this paper, thought has also been given to a different method for a priori calculation of sample size and power. Instead of calculating the estimated number of participants needed for a given research study, one could also work the other way around. After all, many clinical trials depend on the supply of patients within a selective pool and do not have any additional recruiting possibilities. This study, which is no exception to that point, will aim to include a minimum sample of 20 participants during an inclusion period of 18–24 months. A maximum of 30 participants will be included if recruitment is prosperous.

Sample size calculation is usually based on the primary study outcome, which in this study is the difference in CNC word recognition (test-retest at 65 dB SPL) between the experimental and standard CI setting after 6 months of rehabilitation. Using the concept of effect size as interpreted by Cohen’s d [64, 65], the following formula could be used to calculate sample size for a paired *t* test:

$$ \mathrm{N}=2+\left({\left({\mathrm{Z}}_{1-\upalpha /2}+{\mathrm{Z}}_{1-\upbeta}\right)}^2/{\mathrm{d}}^2\right) $$where N = sample size, *α* = type 1 error, *β* = type 2 error, d = effect size*.*

Given the idea of a restricted sample size, it can be argued that it is more valuable to rearrange this formula as to calculate effect size.
$$ \mathrm{d}=\surd \left(2+\left({\left({\mathrm{Z}}_{1-\upalpha /2}+{\mathrm{Z}}_{1-\upbeta}\right)}^2\right)/\mathrm{N}\right) $$

As a result, different outcomes in effect size can be calculated with a sample size range of 20–30 participants, an alpha range of 0.01–0.08 and a given power of 0.08. When considering a type 1 error of 0.05 and a sample size of 20, an effect size of 0.66 or larger can be detected. If 30 study participants are recruited and the alpha level is kept similar, the resulting detectable effect size is at least 0.53.

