### Development of an alternative trial design

To counteract current limitations in CI research, we believe an alternative methodology that allows for experimental interventions in a prospective trial setup is necessary. We therefore propose a study design for a clinical trial that is feasible, takes a within-subject perspective, and in which the participants are their own control. This design is similar to the traditional crossover perspective, but uses daily crossover randomization as a method for simultaneous utilization of study conditions instead of a crossover in subsequent, consecutive periods. By using daily crossover randomization, participants may switch between control and intervention on a daily basis. This is followed by a period of free choice between both conditions to incorporate participant preference. It is proposed that this new approach will facilitate data collection from small sample sizes, reduce the impact of individual subject characteristic variability, decrease the number of subjects needed to find a moderate statistical effect, address initial brain plasticity, and prevent the occurrence of a first-order carryover effect.

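### The sample-size section states a power of 0.08 and inverts its own formula wrongly; the reported 0.66 and 0.53 are right only at power 0.80 with 20 and 30 analysed pairs

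*Protocol article*

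**What the plan says.** The Sample size section takes the number of participants as given by patient supply. The study "will aim to include a minimum sample of 20 participants during an inclusion period of 18–24 months", and "A maximum of 30 participants will be included if recruitment is prosperous". For a paired t test on the 6-month difference in CNC word recognition, the section gives N = 2 + (Z(1−α/2) + Z(1−β))²/d². It then states that "it can be argued that it is more valuable to rearrange this formula as to calculate effect size" and prints d = √(2 + (Z(1−α/2) + Z(1−β))²/N).

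The inputs are described as "an alpha range of 0.01–0.08 and a given power of 0.08". The results are: "When considering a type 1 error of 0.05 and a sample size of 20, an effect size of 0.66 or larger can be detected", and for 30 participants at the same alpha "the resulting detectable effect size is at least 0.53".

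Other sections determine who is left to analyse:
- **Design, setting and recruitment:** consent and inclusion take place no later than one week before surgery.
- **CI frequency mapping:** a participant who cannot be assigned at least 8 channels is taken out of the study. This depends on the CBCT, which is made after surgery.
- **Compliance:** severe non-compliers are removed from the intention-to-treat population.
- **Statistical methods, data reporting and analysis:** the intention-to-treat population is the one analysed.

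**The concern.** A reader who follows the section as printed cannot arrive at its results. The power is a tenth of the conventional value. The rearranged formula is not the algebraic inverse of the one above it, because the 2 should be subtracted from N and has instead become a separate term under the root. The article presents this reversed calculation as a method suited to trials with a restricted pool of patients, so others may apply the printed equation and obtain a detectable effect more than twice the correct one.

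The calculation also enters 20 and 30 as if every included participant contributes a pair to the primary comparison, while the article itself provides for removals after inclusion. If pairs are lost, the smallest effect detectable at 80% power is larger than stated.

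**Working it through.** **Inputs (Sample size section).** N = 20 and 30; alpha 0.05, two-sided because the formula uses Z(1−α/2), so Zα = 1.960; printed power 0.08. Write c = (Zα + Zβ)².

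**Step 1. Reproduce the stated figures.** Solving N = 2 + c/d² for d gives d = √(c/(N − 2)). With power 0.80, Zβ = 0.8416 and c = (1.960 + 0.8416)² = 7.849.
- N = 20: √(7.849/18) = 0.660.
- N = 30: √(7.849/28) = 0.529.

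These are the stated 0.66 and 0.53. In the forward direction, d = 0.66 returns N = 20.02 and d = 0.53 returns N = 29.94. The exact power of the paired t test (noncentral t) gives 0.6604 and 0.5292, so the approximation is adequate.

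**Step 2. Try what is printed.** With power 0.08, c = 0.308.

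| Formula | Power | N = 20 | N = 30 |
|---|---|---|---|
| Correct inversion, √(c/(N − 2)) | 0.80 | 0.66 | 0.53 |
| Correct inversion, √(c/(N − 2)) | 0.08 | 0.13 | 0.10 |
| Printed, √(2 + c/N) | 0.80 | 1.55 | 1.50 |
| Printed, √(2 + c/N) | 0.08 | 1.42 | 1.42 |

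The printed form has a floor of √2 = 1.41 for any N, alpha or power, so it cannot return 0.66 or 0.53 under any inputs.

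**Step 3. Rule out a misplaced bracket.** At power 0.80, √((2 + c)/N) gives 0.70 and 0.57, and √(c/N) gives 0.63 and 0.51. Neither matches. Of the forms tried, only the correct inversion at power 0.80 does.

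**Step 4. Included versus analysed.** The article gives no loss rate, so the losses below (10% to 20%) are assumptions. Detectable d is at 80% power and two-sided alpha 0.05; power is from the exact paired t test.

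| Included | Analysed | Detectable d | Power at the stated d |
|---|---|---|---|
| 20 | 20 | 0.66 | 80% at 0.66 |
| 20 | 18 | 0.70 | 75% at 0.66 |
| 20 | 17 | 0.72 | 72% at 0.66 |
| 20 | 16 | 0.75 | 69% at 0.66 |
| 30 | 30 | 0.53 | 80% at 0.53 |
| 30 | 27 | 0.56 | 76% at 0.53 |
| 30 | 24 | 0.60 | 70% at 0.53 |

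**The case against.** The best defence is that these are slips in transcription. The first formula is correct, power 0.80 is the conventional value, and together they give both stated results to two decimals. The authors evidently did not compute with 8% power or with the misprinted equation, and the numbers 1.55, 1.50, 0.13 and 0.10 appear nowhere in the article. This stands, and it limits the weight of the point. It does not remove it: the section states a wrong power and a wrong formula, and the reader has to repair both to recover the result.

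On analysed pairs, the full research protocol is not shown and could contain a loss allowance or replacement rule. Also, 20 is a minimum with room up to 30, so 16 to 18 analysed arises only if recruitment ends near the floor. This also stands, so that part is a conditional caveat.

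A reader might infer more than the article supports:
- **That the 20 to 30 participants lose their justification.** The section sets N by patient supply and derives the effect size from it, so correcting the formula leaves N untouched.
- **That alpha is left open.** The range of 0.01 to 0.08 describes a set of scenarios; both reported effect sizes are tied to 0.05.
- **That the trial promises adequate power for a moderate effect and misses it.** The claim, in Development of an alternative trial design, that the approach will "decrease the number of subjects needed to find a moderate statistical effect" compares designs. It gives no numerical effect size and no power.

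**Conclusion.** The power of 0.08 and the rearranged formula are both wrong as printed, and neither yields the reported results. The results themselves, 0.66 and 0.53, are correct for power 0.80, two-sided alpha 0.05 and 20 or 30 analysed pairs. This is a minor to moderate error in the stated method; it affects neither the design nor enrolment.

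The secondary caveat is that the figures hold only if every included participant is analysed. With an assumed loss of 10% to 20%, the detectable effect rises from 0.66 to between 0.70 and 0.75 when 20 are included, and from 0.53 to between 0.56 and 0.60 when 30 are included. The size of this shift rests entirely on the assumed loss.

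**What to change.** In the Sample size section:
1. Replace the rearranged formula with d = √((Z(1−α/2) + Z(1−β))²/(N − 2)).
2. State the power as 0.80.
3. State that 0.66 and 0.53 apply to 20 and 30 analysed pairs at the 6-month primary comparison.
4. Add the detectable effect for fewer analysed pairs, labelled as an assumed range: 0.70, 0.72 and 0.75 for 18, 17 and 16 of 20 included; 0.56 and 0.60 for 27 and 24 of 30 included. If the full protocol gives an expected loss or a replacement rule, use that instead.

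This is a change of text only. Enrolment, endpoint and analysis stay as they are. The cost is that the stated detectable effect becomes slightly less favourable once losses are shown.

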### Statistical methods, data reporting and analysis

The outline of this study can be categorized in multiple phases, each concerning different statistical outcomes, listening conditions and endpoints. The statistical analysis plan will be finalized before the database lock. In general, analyses will be carried out for each treatment option (experimental fitting versus standard fitting for both CI and hearing aid), for different outcomes (e.g. word recognition, subject preference, quality of life) and different listening conditions (with CI, hearing aid or bimodal). The main statistical analysis will focus on the question of whether the experimental fitting, based on individual imaging and tonotopical fit, will give rise to improved outcomes in word recognition compared to the standard fitting. Learning curves will be analyzed by calculating steepness and area under the curve. Normality will be assessed by examining histograms, Q-Q plots, and performing the Shapiro-Wilk test. Depending on whether normality can be established, either nonparametric or parametric statistical comparison tests will be performed. Analysis will be performed in all participants in the intention-to-treat population with separate reporting of participants who are included on a per-protocol basis. Results of these different outcomes will be presented as mean, standard deviation and percentile distribution. In the case of non-parametric testing, results will also be presented as median and interquartile range.

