## Methods/design

### Design, setting and recruitment

This study is a single blinded, controlled clinical trial with daily crossover randomization, which will be implemented directly from the start of the CI rehabilitation process. Its protocol has been approved by the ethics committee of the Maastricht University Medical Center (MUMC+)(NL64874.068.18 / METC 18–028) and has been registered at clinicaltrials.gov (NCT03892941).

A minimum of 20 and a maximum of 30 participants will be included, with a 1-year follow-up period after first fitting. The study outline can be classified in 3 different phases (Fig. 1). During phase 1, starting at first fit, CI optimization will take place during which subjects follow a randomization scheme whereby each individual crosses over between the experimental and standard fitting program. A period of free choice follows in which patients have the liberty of choosing whatever program they prefer, thereby incorporating patient preference as an outcome in the trial design. In phase 2, starting at 6 months after first fit, those participants who choose to retain a hearing aid in the contralateral ear will receive an experimental fitting of their HA based on loudness scaling. Participants that do not wear a contralateral hearing aid, or who have worn their hearing aid less than half of their CI wearing time, will receive no intervention during phase 2. During phase 3, starting at 8 months after first fit, participants will receive the final fit of their CI and their hearing aid based on the preferences they have obtained during phase 1 and phase 2.

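### Normality checks on 20 to 30 participants choose between the t test and a rank test for the main CNC comparison, so the hypothesis and p-value depend on a noisy pre-test

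*Protocol article*

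**What the plan says.** The section on statistical methods, data reporting and analysis gives a two-step rule. First, "Normality will be assessed by examining histograms, Q-Q plots, and performing the Shapiro-Wilk test". Then, "Depending on whether normality can be established, either nonparametric or parametric statistical comparison tests will be performed". It states no cut-off for Shapiro-Wilk and no way to combine the test with the two visual checks. The same paragraph names word recognition, experimental against standard fitting, as the main question and does not exempt it. It also says that the statistical analysis plan will be finalised before database lock.

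The sample size section defines the primary outcome as "the difference in CNC word recognition (test-retest at 65 dB SPL) between the experimental and standard CI setting after 6 months of rehabilitation". It bases the calculation on one test: "the following formula could be used to calculate sample size for a paired" t test. On recruitment, the design section says "A minimum of 20 and a maximum of 30 participants will be included".

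**The concern.** A paired t test concerns the mean difference between maps. A Wilcoxon signed-rank test concerns the pseudomedian, the centre of the pairwise averages of the differences. The two coincide when the differences are symmetric and part when they are skewed, and skewed data are what the pre-test is meant to detect. The rule therefore changes the question in the situation where the change matters.

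With 20 to 30 differences Shapiro-Wilk detects moderate skew only some of the time. Two trials of the same population could then test different hypotheses because of sampling noise. The stated detectable effects cover the t-test branch only. At stake are a main p-value whose meaning is not fixed in advance and, if the differences are skewed, a type I error above 5% for the mean difference on which the trial was sized.

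**Working it through.** **1. Reproduce the plan's figures.** The article's formula is N = 2 + (z_{1-α/2} + z_{1-β})²/d². Solved for d, it is d = √[(z_{1-α/2} + z_{1-β})²/(N − 2)]. With two-sided α = 0.05 and power 0.80, the squared sum is 7.849.
- N = 20: √(7.849/18) = 0.660, which matches "an effect size of 0.66 or larger can be detected".
- N = 30: √(7.849/28) = 0.529, which matches the stated 0.53.

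Exact noncentral-t power is 79.9% for d = 0.66 at N = 20 and 80.1% for d = 0.53 at N = 30. The figures therefore belong to a two-sided paired t test. The printed "a given power of 0.08" and the printed rearranged formula do not reproduce them (power 0.08 gives 0.13 and 0.10; the printed formula gives 1.55 and 1.50). That is a separate matter and does not affect this point.

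**2. Inputs to the simulation.** From the article: 20 or 30 paired differences, two-sided α = 0.05, and the selection rule. Assumed, because the article does not give them: a Shapiro-Wilk cut-off of p < 0.05 (below it exact Wilcoxon signed-rank, otherwise paired t), and the shape of the differences, taken over a range. The visual checks cannot be simulated. Each tabulated scenario used 20,000 samples (standard error about 0.15 to 0.25 percentage points).

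**3. Symmetric differences** (normal, uniform, Laplace, t with 3 df). The two-stage rule rejects in 4.8% to 5.3% of trials at N = 20 and 4.8% to 5.0% at N = 30. There is no material inflation.

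**4. Skewed differences, true mean difference zero.** Shapiro-Wilk rejection rate (SW), then rejection of the mean null by the two-stage rule against the t test alone:

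| Shape (skewness) | SW, N=20 | Two-stage v t, N=20 | SW, N=30 | Two-stage v t, N=30 |
|---|---|---|---|---|
| Gamma, shape 4 (1.0) | 29% | 7.3% v 6.0% | 45% | 7.5% v 5.5% |
| Gamma, shape 2 (1.4) | 53% | 9.1% v 6.8% | 75% | 11.0% v 6.5% |
| Lognormal, σ 0.5 (1.75) | 52% | 9.9% v 7.3% | 72% | 11.6% v 6.7% |
| Exponential (2.0) | 83% | 13.0% v 8.2% | 97% | 16.3% v 7.4% |

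At skewness 0.5 and N = 20 the figures are about 5.3% v 4.9%. Repeat runs differ by a few tenths of a point; at skewness 1.4 and N = 30 they lie between about 10% v 6% and 11% v 6.5%.

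At N = 20 and skewness 1.4 the choice of test is close to a coin toss. At N = 30 the rule is further from 5% in every row, while the t test alone is closer to it. Recruiting to the planned maximum therefore does not help.

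**5. The same shapes, pseudomedian difference zero** (the signed-rank test's own null). The two-stage rule rejects in 5.9% to 6.0% at N = 20 and 5.9% to 6.4% at N = 30. Wilcoxon alone rejects in 5.1% to 5.6%. On this yardstick the excess is about 1 point or less.

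**The case against.** Several parts of the case on the other side stand.

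- **The inflation is conditional.** If the map makes no difference in any participant, the paired differences are symmetric and the rule holds about 5%. Up to skewness 1.0 at N = 20 the excess over the t test is about 1 point or less in most runs (1.3 points in the table). The article gives no distribution for the CNC differences. Uneven benefit is plausible, since the pilot frequency shift averaged 1.36 octaves with SD 0.56, but that does not establish skew in the scores.
- **The yardstick matters.** Much of the excess in step 4 arises because a rank test is judged against a mean hypothesis. The mean is still the relevant yardstick here, because the sample size rests on it.
- **Only the test and the p-value switch.** A reader might infer that the reported effect changes as well. The article reports mean and SD in all cases and adds median and interquartile range when nonparametric tests are used.
- **Disagreement between the tests is not the cost of the rule.** A reader might count how often always-t and always-Wilcoxon disagree, about 6% for normal data at d = 0.5 and N = 20. The two-stage result differs from t alone in only about 0.6% of such trials.
- **Blinding.** A reader might infer that an unblinded analyst picks the test by eye. The article says that participants are blinded and is silent on the analyst, so this is not supported.

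It can also be said that the paragraph speaks in general terms, does not tie the normality check to the paired differences, and leaves detail to an analysis plan that is not shown. Applying the check to the paired differences is an inference, though the natural one given the paired t test. The deferral to the analysis plan does not remove the point: the article already states a data-driven selection rule without exempting the main comparison, and a plan that follows it would inherit the rule.

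**Conclusion.** The point holds in a limited form. The rule as written leaves the hypothesis for the main CNC comparison to a pre-test with little power at N = 20 to 30, while the sample size assumes the paired t test. This follows from the text without simulation.

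The effect on error rates runs from nil (symmetric differences) through about 1 point at skewness 1.0 to about 5 points at skewness 2.0, for the mean null at N = 20 and relative to the t test alone. At N = 30 the excess is 2.0 points at skewness 1.0 (7.5 − 5.5) and 8.9 points at 2.0 (16.3 − 7.4). Against the pseudomedian null the rule gives about 6%. These sizes rest on the assumed shapes, the assumed 0.05 cut-off and the reading that the check is made on paired differences. Unconditional inflation is not supported. The change is worth making because it is cheap and settles what is being tested.

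**What to change.** For the primary 6-month CNC difference, pre-specify the paired t test of the mean difference with a 95% CI, whatever the normality checks show. Report the Wilcoxon signed-rank test as a named sensitivity analysis. Keep histograms, Q-Q plots and Shapiro-Wilk as description only.

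This takes about one sentence in the analysis plan before database lock. Both tests are still reported, and 0.66 and 0.53 stay valid for the test actually used. The downside is that the t test itself exceeds 5% under strong skew (about 7% to 8% in the scenarios above) and may lose some power if the differences are heavy-tailed. The signed-rank result alongside would let readers see either problem.

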### Ethics

Health risks specifically associated with study participation are limited to exposure to ionizing radiation from cone beam CT. However, participants will be required to devote their time, effort and attention to the study. Specifically, during rehabilitation participants will be trained in two different CI fitting programs instead of one. It is unclear whether this will be a disadvantage or a benefit, as it most likely depends on individual brain plasticity mechanics. From an ethical perspective, however, it can be noted that the possible burden of adapting to two CI fittings simultaneously will be limited to a time window of 12 weeks, after which the effects of wearing two fittings at the same time can be expected to wash out.

## Discussion

The ELEPHANT study combines an individualized cochlear implant fitting strategy with new ideas on clinical trial setups. The study design presented may be regarded as a suitable alternative to the RCT that resolves challenges related to this conventional trial setup (e.g. the number of participants) in this specific setting. By using a daily-randomized crossover setup, our approach aims to remove bias introduced by age, cognition, prior speech performance, pathology and duration of hearing loss, that are present in a normal RCT. Compared to traditional crossover designs, the proposed approach is expected to obtain more information from smaller sample sizes, and to prevent possible first-order carryover effects. In the current protocol, both the efficacy of the trial design and, as an experimental object, a CI fitting strategy based on post-operative imaging will be evaluated. Also, an experimental HA fitting based on loudness perception will be evaluated.

### Study design

Here we propose daily crossover randomization as a strategy to prevent first-order carryover effects due to initial brain plasticity related to the intervention that was given first. Although there is limited neuroimaging research on the cortical reorganization after CI implantation because of technical challenges and safety concerns [66], results of behavioral studies indicate that plasticity occurs predominantly during the first critical period of rehabilitation: the largest performance gain with a CI occurs in the first months of use [33, 67]. Thus, as initial plasticity related to the first intervention has already occurred by the time the second intervention is presented, it is likely that participants are biased towards the first intervention.

One limitation of using daily randomization as proposed here, is that the distribution of exposure to either control or intervention will differ according to each randomization scheme. However, it has been shown that this is not expected to significantly affect the end result as the total duration of exposure is more relevant than the distribution of exposure over time [68]. One could also argue that the absolute learning speed of either mapping approach at the same time will be lower because the exposure is distributed over twice the amount of time, leading to a prolongation of the rehabilitation phase. This is certainly not a given, and the opposite might even be true. Effects of transfer of information from two different maps may increase learning rates in both maps [69]. Interestingly, it has been shown that different transfer functions can be represented simultaneously within the auditory system. In a sound localization experiment, the spectral spatial cues of subjects were disrupted by altering the shape of their pinnae with molds [70]. Although sound localization was initially disrupted, subjects were able to reacquire localization skills while wearing their molds and reach performance levels close to normal. Despite this adaptation, localization accuracy was unaffected in undisturbed ears. Thus, it is apparently possible for the human auditory system to acquire new representations of sound location without interfering with an already existing set. Furthermore, on a neural level it has been shown that task performance can induce rapid plasticity in primary auditory cortex [71–73], indicating that auditory neural processing is flexible and can quickly adapt to changing circumstances. It seems conceivable that similar effects will occur while learning to hear with two different CI fittings.

Importantly, in our design, subjects will not be allocated to the same program for more than 2 days consecutively in the first time-window and no more than 4 days consecutively in the second time-window. The aim of this was to prevent the development of a fixed preference to any program that is given most during the first period of rehabilitation (i.e. either the experimental or standard program). Specifically, based on an analysis of clinical data within Maastricht UMC+ and published studies [32, 35] two distinct time periods have been roughly defined in the learning curve of patients with CI. The first 4 weeks of CI rehabilitation constitute the first time-window as they appear to be characterized by a large improvement in word recognition. Thus, this first period of adaptation can be considered crucial in the learning process. Therefore, a predominance of either the standard or experimental program during this time window will have a major impact on the preference for one or the other. CI rehabilitation tends to show a more flattened learning curve after 4 weeks (second time-window). Thus, by limiting the allocation to the same program to a maximum of 2 days consecutively in the crucial first 4 weeks, and no more than 4 days consecutively thereafter, we avoid the development of a fixed preference based on exposure time.

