### Daily-randomization procedure

In this new type of trial design subjects act as their own control and treatment allocation is based on daily randomization. Two speech processors (physically labeled with either a green circle or a purple triangle) will be given to each participant, one of which will be programmed with the experimental settings and the other with the standard settings. Each day, subjects will be allocated to wear one of the two processors for a period of 3 months. A scheme with corresponding labels will be provided for each participant (Fig. 2). By equipping participants with two different processors, instead of one processor with FAT settings on different program slots, it is thought that issues with compliance are less likely to occur.

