**Fig. 2 Fig2:**
[figure not shown]
Example of a daily-randomization scheme. Green and purple labels indicate which cochlear implant (CI) processor to wear

To prevent subjects from developing a preference for one of both programs during the first crucial period of adaptation to the cochlear implant, several prerequisites have been included in the randomization procedure. First, the same processor will not be allocated for more than 2 days consecutively within the first 4 weeks of CI rehabilitation. This restriction will be broadened from 4 weeks on to a maximum of 4 days consecutively. Second, to aid blinding of the participant to the intervention and in order to prevent subjects habitually preferring one processor to the other, the assignment of the two fittings across the two processors is randomized by the fitting clinician. As a result, there is a 50% chance that the experimental program will be saved on either the green or purple processor at each fitting. Participants will be blinded in that they are unaware which CI processor contains the experimental setting at any point in time. During the fitting procedures, participants will not be given any visual or verbal cues that may lead to recognizing which processor contains which settings.

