### Compliance

In the first 3 months of the study, participants are required to wear their CI processors according to their personal randomization schedule. They should also wear their contralateral hearing aid for at least 50% of the CI wearing time over the course of the first 6 months, in order for the subject to be included for the experimental hearing aid fitting. Participants are asked to report the wearing time of both their CI processors and their hearing aid in daily diaries. By comparing these values to the ratios in the randomization schedule, differences in compliance will be calculated at regular intervals over each time window and compared to a set of cut-off points (see Additional file 1: research protocol). Since data logging features are not currently available in the CI research fitting software BEPS+, the only check on reliability of patient diary reporting is through the data logging of the hearing aid in Phonak Target. In the case of minor randomization deviations, participants will be treated as protocol deviators and will be removed from the per-protocol analysis population. In the case of severe non-compliance with randomization procedures, participants will be removed from the intention-to-treat analysis population.

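### The consecutive-day caps limit runs, not total days per map, so they reduce exposure imbalance but do not exclude it as the Discussion says (minor)

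*Protocol article*

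**What the plan says.** Methods, Daily-randomization procedure, sets the exposure: "Each day, subjects will be allocated to wear one of the two processors for a period of 3 months". The Ethics section puts the same period at 12 weeks ("will be limited to a time window of 12 weeks"). Two restrictions on the sequence are stated: "the same processor will not be allocated for more than 2 days consecutively within the first 4 weeks of CI rehabilitation", and then "This restriction will be broadened from 4 weeks on to a maximum of 4 days consecutively". The map-to-processor link is also redrawn at each fitting. The article states no rule on the total number of days per processor or per map.

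The Discussion (Study design) gives the reasoning. It concedes that exposure will differ between schemes and sets this aside because "the total duration of exposure is more relevant than the distribution of exposure over time". It then says of the first 4 weeks that "a predominance of either the standard or experimental program during this time window will have a major impact on the preference" for one program or the other, and concludes from the two caps that "we avoid the development of a fixed preference based on exposure time".

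The Compliance section measures adherence against each participant's schedule ("By comparing these values to the ratios in the randomization schedule") without giving the ratio.

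**The concern.** Predominance and exposure time are totals; the caps restrict run lengths. A sequence can obey both caps and still give one map more days than the other, so the stated rule does not secure the stated property. The argument that total duration outweighs its distribution in time reassures only if the totals are equal, and no stated rule makes them so.

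Two maps are being learned in parallel, so unequal practice would add noise to each person's paired difference during phase 1. On the protocol's own reasoning it could also shift that person's preference. Table 2 lists preference as a primary outcome, and preference informs the final fit in phase 3. The planned sample is only 20 to 30.

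**Working it through.** The article gives no figure for exposure balance, so there is nothing to reproduce. The check asks what the stated caps allow and what they typically produce.

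**Inputs.** Run cap of 2 for days 1-28 and 4 from day 29 (Daily-randomization procedure). Period of 84 days, taking 12 weeks from the Ethics section. The generating rule is not stated. Two are assumed: (a) a fair coin each day with a forced switch at the cap; (b) a uniform draw over all sequences that meet the caps.

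**What the caps permit.**
- Weeks 1-4: AAB repeated nine times plus one A is 28 days, with A = 9 × 2 + 1 = 19 and B = 9, so 19:9.
- Weeks 5-12: AAAB, then AAAAB ten times, then AA is 4 + 50 + 2 = 56 days, with A = 3 + 40 + 2 = 45 and B = 1 + 10 = 11. The opening AAA follows one A on day 28, a run of 4, which is allowed.
- Together: 19 + 45 = 64 against 9 + 11 = 20.

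**What the caps typically produce.** Exact enumeration over last label, current run length and days so far on A gives the distribution of days on one label. The gap is |days on A − days on B|.

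| | Rule (a) | Rule (b) |
|---|---|---|
| Week 4: SD of days on one label | 1.2 | 1.2 |
| Week 4: mean gap (days) | 1.8 | 1.8 |
| Week 4: exactly 14:14 | 33% | 33% |
| Week 4: 16:12 or worse | 19.4% | 20.0% |
| Week 4: 17:11 or worse | 2.8% | 3.0% |
| Week 12: SD of days on one label | 3.1 | 2.9 |
| Week 12: mean gap (days) | 5.0 | 4.7 |
| Week 12: exactly 42:42 | 12.6% | 13.4% |
| Week 12: 45:39 or worse | 42.6% | 39.6% |
| Week 12: 46:38 or worse | 26.4% | 23.4% |
| Week 12: 48:36 or worse | 7.8% | 6.0% |

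Under rule (a) the permitted extremes have probability about 2 in 100,000 (19:9) and about 6 in 10^18 (64:20). With no cap, the week-4 SD would be √(28 × 0.25) = 2.65 days, so the 2-day cap more than halves it.

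**Processor versus map.** These figures apply to the label that the caps act on. If the caps act on processors and the map is redrawn between processors weekly (an assumed interval), simulation puts 16:12 or worse at map level at about 26% by week 4.

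**The case against.** The strongest reply is that the generating rule has not been seen. The article refers to the full research protocol as Additional file 1, and the example scheme in Fig. 2 is not shown. A rule on totals may exist there, and a schedule ratio of 1:1 would fit the Compliance wording as well as any other. The Discussion also speaks of exposure spread over twice the time, which suggests that roughly equal halves were intended. This stands, and it makes every typical figure above conditional. It does not rescue the inference as printed, which credits the caps alone.

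The second reply is that the imbalance is small where the protocol says it matters most. In weeks 1-4 about 97% of schemes are 16:12 or closer under rule (a). The wider gaps build up later, when the article describes a flatter learning curve. This also stands: the caps do much of what they were meant to do.

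Third, the word-recognition comparison in the Sample size section is at 6 months, after a free-choice period as long as the randomized one, in which use may go largely to one map by design. A scheduled gap of a few days is small beside that, and the final fit likewise draws on preference formed through free choice. The article gives nothing that converts days of use into word score, so no loss of precision can be shown.

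**Conclusion.** The point holds as a minor one. The sentence in the Discussion claims more than the stated rule delivers: the caps limit exposure imbalance but do not exclude it. If the caps are the only constraint, the expected consequence is a gap of about 2 days at week 4 and about 5 days at week 12, which adds modest person-level noise to phase 1 learning curves and preference.

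A reader might infer more, and the documents do not support it. The 19:9 and 64:20 splits are admissible but practically never arise under a random draw, so they do not describe the trial. Nor is there systematic bias towards either map: the rules treat the two labels alike, so the imbalance is random in direction across participants. Damage to the 6-month comparison cannot be claimed either, since its size cannot be derived from the article.

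The figures rest on random generation subject only to the caps and on an 84-day period. A balance rule in the full research protocol would remove the numerical concern and leave only the wording.

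**What to change.** First check the full research protocol for a rule on total days. If there is one, cite it beside the claim.

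If there is none:
- Keep the run caps and add a total-days constraint at map level: 14:14 in weeks 1-4 and 42:42 by week 12.
- Where the map-to-processor link changes at a fitting, issue a calendar for the following interval that preserves the planned map sequence.
- For schemes already issued (recruitment began in March 2019), report scheduled days per map and use the day difference as a covariate in a sensitivity analysis of the paired comparison.
- Reword the Discussion to say that the caps limit exposure imbalance.

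The cost is a change to the program that generates the schedules and a new calendar at each reassignment. The last day or two of a balanced block become slightly more predictable, which matters little while participants do not know which processor carries which map.
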